**(8) Change in 12-item Short Form Health Survey (SF-12)**

[ Time Frame: Change from baseline at 4 weeks, *8 weeks* and 16 weeks]

The SF-12 is a generic health-related quality of life measure.

**(9) Blinding assessment**

[ Time Frame: At weeks 4 after randomisation.]

To test whether the participants are blinded successfully, all participants will be asked to guess which kind of *treatment* they received.

**(10) Credibility/Expectancy Questionnaire**

[ Time Frame: About 5 min after the first treatment]

The credibility and expectancy of participants will be measured using the Credibility/Expectancy Questionnaire.

**(11) Rescue medicine**

*[ Time Frame: At weeks 4, 8 and 16 after randomisation.]*

*Any use of pain-killers will be ascertained.*

**Table 4. Information collection content and time frame**

| Measures /Event                                 | Selection /baseline - 1 st | Week 4 - 2 nd        | Week 8 - 3 rd        | Week 16 - 4 th       |
|-------------------------------------------------|---------------------------------------|---------------------------------|---------------------------------|---------------------------------|
| Collection time range                    | Week -1 or Week 0                     | Within one week before or after | Within one week before or after | Within one week before or after |
| Informed Consent Form                    | X                                     |                                 |                                 |                                 |
| Basic Information                        | X                                     |                                 |                                 |                                 |
| WOMAC                                    | X                                     | X                               | X                               | X                               |
| NRS                                      | X                                     | X                               | X                               | X                               |
| PGA                                      | X                                     | X                               | X                               | X                               |
| OARSI Responder Criteria                 |                                       | X                               |                                 |                                 |
| Change in 30 second time chair rise test | X                                     | X                               |                                 |                                 |
| Change in Timed Up and Go Test Time      | X                                     | X                               |                                 |                                 |
| Change in One Leg Standing Test          | X                                     | X                               |                                 |                                 |
| SF-12                                    | X                                     | X                               | X                               | X                               |
| Blinding assessment                      |                                       | X                               |                                 |                                 |
| Credibility/Expectancy Questionnaire     | X                                     |                                 |                                 |                                 |
| Rescue medicine                          |                                       | X                               | X                               | X                               |
| Adverse events                           |                                       | X                               |                                 |                                 |

## Blinding

### Double (Evaluators and Patients)

During the implementation stage, besides only the evaluators are blinded and they can't participate in the screening, recruitment scheduling, and treatment. The patients will be informed that they will receive manual therapies, but without detailed information about whether they will receive traditional Tuina or modern mPT. And at the end of the trial, the blinding questionnaire will be conducted to assess the success of blindness. In a short, patients, evaluators and statisticians will be blinded to the group assignment in this trial.

## **Additional file 2-Complete list of Inclusion Criteria and Exclusion Criteria**

### **Inclusion Criteria**

- (1) radiologic confirmation of osteoarthritis (Kellgren-Lawrence score II or III) in recent 3 months,
- (2) a pain score of at least 4 points on the numeric rating scale (NRS) (range:0-10; higher scores indicate greater pain),
- (3) single/bilateral knee pain, and a duration of knee joint pain at least 6 months.

### **Exclusion Criteria**

- (1) The patient has a history of knee surgery or is willing to perform knee surgery (Total Knee Arthroplasty or knee arthroscopy);
- (2) Knee pain caused by other diseases (such as joint bodies, the severe effusion of joint cavity, infection, malignant tumors, autoimmune diseases, trauma, etc.);
- (3) Oral administration of hormones within 3 months, intra-articular injection within 6 months, knee injuries or open injuries within 6 months, or knee arthroscopy within 1 year;
- (4) Severe acute/chronic organic or mental diseases;
- (5) Pregnant women, pregnant and lactating women;
- (6) Coagulation disorders (such as hemophilia, etc.), or the skin diseases at the site of operation;
- (7) Instrument support therapy for patients with knee osteoarthritis disability;
- (8) Participation in another clinical study in the past 3 months;
- (9) History of receiving acupuncture, massage, manipulation, or any medical plaster treatment within 3 months;
- (10) Breaks for treatment longer than 3-4 weeks, depending on each circumstance or merit may be construed as non-compliance and may be excluded.

### **Additional file 3- The response rate defined by the Outcome Measures in Rheumatology Clinical Trials and Osteoarthritis Research Society International (OMERACT-OARSI)**

The response rate was defined as the proportion of patients who achieved the following criteria at week 4: 1)  $\geq 50\%$  improvement in WOMAC-pain or WOMAC-function and an absolute improvement of  $\geq 20$ , or 2) improvement in at least 2 of the following 3: 20% improvement in pain and absolute change  $\geq 10$  on WOMAC-pain, 20% improvement in pain; absolute change  $\geq 10$  on WOMAC-function; or moderate or greater improvement ( $\leq 4$ ).

## **Additional file 4-Statistical Analysis Plan**

### **1. Trial Design**

This is a single-center parallel active-controlled, blinded randomized controlled trial of comparing Chinese Tuina therapy and manual physical therapy (mPT) for patients with KOA. This trial aims to validate the effectiveness and safety of Tuina for KOA compared with mPT.

### **2. Timing of outcome assessments**

Outcomes are collected at baseline, week 4, week 8 and week 16.

### **3. Interim analyses**

There are no interim analyses in this study.

### **4. Level of statistical significance and Confidence intervals to be reported**

All applicable statistical tests will be 2-sided and will be performed using a 5% significance level. All confidence intervals will be 95% confidence intervals.

### **5. Analysis Populations**

The primary analysis will be based on the principle of intention-to-treat (ITT), defined as all available data from all randomized patients were originally assigned, regardless of their adherence to their assigned treatments.

### **6. Data of Trial Population**

**Screening Data** Screening data will be collected and summarized in text and/or flow diagram, the following summaries will be presented as below: the recruitment timeline, the number of participants assessed for eligibility screened, the number of participants recruited, the number of participants excluded, and the reasons for exclusion.

**Recruitment** The number of people enrolled, randomized, allocated to each treatment group, lost to follow up (including reasons) and analyses will be presented in the flow diagram.

**Baseline Characteristics** Baseline characteristics will be summarised and presented in a table:

- Age, Sex, BMI (kg/m^2), Race
- Duration (Months), Kellgren criteria, Target knees
- Education, Working status, Marital status
- Concomitant disease
- History of treatment, the Satisfaction of Previous Treatment
- WOMAC, NRS, SF-12
- 30 second time chair rise test, Timed Up and Go Test Time, One Leg Standing Test
- Credibility/Expectancy Questionnaire

Baseline characteristics will be summarized as appropriate (means and standard deviations for continuous variables for normal distribution, medians and interquartile ranges for abnormal distribution, counts and percentages for categorical variables). Tests of statistical significance will not be undertaken for comparing baseline characteristics of treatment groups.

### **7. Outcome Definitions**

**Primary Outcome** The change in the total Western Ontario and McMaster University Osteoarthritis Index (WOMAC) from baseline to 4 weeks

**Secondary Outcomes** The secondary outcomes covered pain, physical function, and patients' overall assessment of disease severity.

- **Pain Dimensions** WOMAC pain (the change between the baseline and 4, 8, and 16 weeks), the worst knee pain in the last 24 hour using NRS(the change between the baseline and 4, 8, and 16 weeks) ;

- **Function Dimensions** the average function of previous week using WOMAC function (the change between the baseline and 4, 8, and 16 weeks), WOMAC stiffness (the change between the baseline and 4, 8, and 16 weeks), 30 Second Time Chair Rise Test (the change between the baseline and week 4), Timed Up and Go Test Time (the change between the baseline and week 4), One Leg Standing Test (the change between the baseline and week 4);
- **Patients' overall assessment of disease severity:** the 12-item Short Form Health Survey (the change between the baseline and 4, 8, and 16 weeks), the patient global assessment (the change between 4, 8, and 16 weeks);
- **Criteria of Response Rate:** The OMERACT-OARSI responder criteria to assess the response rate of treatment for KOA at 4 weeks.
- **The blinding assessment**

## 8. Analysis methods

We will use intention-to-treat analyses, analyses will be conducted by a statistician blinded to treatment allocation, with two-sided hypothesis tests. Changes from baseline will be presented for each group at each time point using the mean change and 95% confidence intervals.

**Primary outcome** Primary outcome will apply the repeated measures analysis of variance. Age, sex, BMI, baseline WOMAC score, medication as the covariates. The mean difference in change from baseline to 4 weeks of WOMAC total as the dependent variables, and group (Tuina group and mPT), time (baseline, week 4, 8 and 16), and the group  $\times$  time interaction as independent variables. The approximate normality and Mauchly's test of sphericity were examined. Then the interaction of group-interaction term was tested first. If significant, between-group differences at each time point were tested. If not significant, the treatment main effect was tested next.

**Secondary outcomes** For repeated measures of continuous outcome, including the subscale of WOMAC, NRS, SF-12 and PGA, will be estimated using the repeated measures analysis of variance, 30 Second Time Chair Rise Test, TUG and One Leg Standing Test will be applied with an independent t test for normal distribution, Mann-Whitney U test for unnormal distribution. And for categorical variables- responder criteria, will be compared across groups with the  $\chi^2$  tests or Fisher's exact test.

**Blinding outcome** Blinding assessment will apply the James blinding index with the blinding package of SAS software.

**Effect size** Effect size will be computed with mean group-difference/baseline SD; **MCID** The minimal clinically important difference (MCID) of WOMAC- total is set as 14%, which will be calculated with the change of baseline and the corresponding evaluation time point/baseline

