## **Study Design**

### **1. Overview of Study Design**

This trial is a single-center parallel active-controlled, blinded randomized controlled trial that aims to compare the effectiveness of Tuina and mPT. A total of 140 qualified KOA patients will be randomly divided into either the Tuina group or mPT group at a ratio of 1: 1. In the Tuina group, patients will receive the Tuina therapy, and patients in the mPT group will receive joint mobilization, soft tissue manipulations, passive stretching, and strength training. They will both receive a total of 8 treatments in a 3-week course. Additionally, both groups will be provided health education and home-exercise instruction. Evaluations will be conducted at baseline (week 0) and 4 and 16 weeks. The primary outcome is the related symptoms of KOA, and secondary outcomes include health-related quality of life, treatment satisfaction, physical limitation, emotional and psychological stress, and adverse events. Figure 1 describes the flow chart of these procedures.

The study consists of 5 phases: recruitment, selection, baseline, treatment, and follow-up.

[figure not shown]

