#### 4. The Target Number of Participants and Estimation Basis

- (1) Estimation of the number of patients: The following is assumed using the reference literature of prior studies to estimate the number of patients.
- (2) Level of significance,  $\alpha_{\text{two-sides}} = 0.05$ .
- (3) Type 2 error ( $\beta$ ) is set to 0.2, and the power of the test is set to 80%.
- (4) Based on our pilot study and the previous studies about the minimal clinically important difference (MCID) [28, 29], we assumed that the primary outcome (a total WOMAC score at 4 weeks) in Tuina group was expected to have mean difference of 7 to mPT with a standard deviation for both groups of 13.
- (5) Compliance: 80% (the ratio expected to receive treatment 8 times or more during the 3-week treatment period).
- (6) Sample size calculation for the trial by using PASS 15 (Power Analysis and Sample Size Software (2017). NCSS, LLC. Kaysville, Utah, USA, [ncss.com/software/pass](http://ncss.com/software/pass).)

As a result of applying (1), (2), (3), (4), and effect size, the sample size is calculated to be 140 in total, 70 patients in each group.

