## 10. Missing data reporting and assumptions/statistical methods to handle missing data

Missing data will be handled with the multiple imputation with 20 iterations for the primary outcome. Baseline characteristics of patients who provided the primary outcome and those who did not will be compared using t tests or chi-square tests.

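### Repeated secondary outcomes get classical repeated measures ANOVA and no missing-data method, so by implication one missed visit discards a patient's observed scores for that outcome

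*Supplement*

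**What the plan says.** SAP section 2 sets assessments at baseline and weeks 4, 8 and 16. Section 7 lists the WOMAC subscales, NRS and SF-12 as changes from baseline to weeks 4, 8 and 16, and PGA at weeks 4, 8 and 16.

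Section 8, secondary outcomes: these measures, "including the subscale of WOMAC, NRS, SF-12 and PGA, will be estimated using the repeated measures analysis of variance". No covariates are named for them. The primary-outcome paragraph of the same section pairs this method with Mauchly's sphericity test, and section 11 names SPSS 24.0 as the main software.

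Section 10: "Missing data will be handled with the multiple imputation with 20 iterations for the primary outcome". It gives nothing for secondary outcomes.

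Two statements concern intention to treat. Section 5 applies the principle to the primary analysis and describes it as "defined as all available data from all randomized patients". Section 8 opens with a general commitment to intention-to-treat analyses, placed ahead of both the primary and the secondary paragraphs.

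**The concern.** A sphericity test belongs to the classical ANOVA, in which each patient enters as one complete row of visits. If a cell is empty and nothing fills it, the row is lost. A patient with NRS scores at baseline, week 4 and week 8 but none at week 16 would then contribute nothing to the NRS analysis, not even to the week-4 comparison.

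Two things are at stake. Precision falls because recorded data are thrown away. More seriously, if patients who respond poorly early on tend to miss later visits, and do so differently by arm, the patients left at week 4 are a selected group and the week-4 difference is distorted. A complete-case comparison is unbiased if data are missing completely at random, or if missingness depends only on covariates in the model. For these outcomes the SAP names no covariates.

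There is also an internal oddity. The subscales add up to the total, yet only the total is to be imputed, so one questionnaire would be analysed on different sets of patients.

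**Working it through.** **1. The plan's sample size.** Inputs from the protocol's sample size section: "mean difference of 7 to mPT with a standard deviation for both groups of 13", two-sided alpha 0.05, power 80%, and "Compliance: 80% (the ratio expected to receive treatment 8 times or more during the 3-week treatment period". The formula n = 2(1.96 + 0.84)² × 13² / 7² gives 55 per arm (55.1, so 56, with the t distribution). Dividing by 0.80 gives 69 to 70 per arm, or 138 to 140 in total, against the stated 140. The sample size reproduces and is not affected by this point.

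**2. Documented missingness.** Additional file 5: 7 Tuina and 6 mPT patients lack WOMAC total at week 4, so 13/140 = 9.3%, and 63 + 64 = 127 have it. Additional file 8 shows the same 7 and 6 without a week-4 blinding assessment. This suggests missed visits rather than skipped forms, so NRS, SF-12 and PGA are probably missing too (inference). No figure is given for weeks 8 and 16.

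**3. Excluded against avoidable.** An exclusion is avoidable only if the patient has at least one post-baseline value, because a mixed model recovers no visit for a patient who has none. Baseline is assumed complete. In rows 2 to 4 the 13 are assumed to have no later data.

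| Assumption for weeks 8 and 16 | Calculation | Excluded | Avoidable |
|---|---|---|---|
| Same 13 miss every visit | 13/140 | 13 (9.3%) | 0 |
| Further 5% of the 127 lost | 140 − 127 × 0.95 = 19.4 | 19 (13.8%) | 6 |
| Further 10% lost | 140 − 127 × 0.90 = 25.7 | 26 (18.4%) | 13 |
| Further 15% lost | 140 − 127 × 0.85 = 32.1 | 32 (22.9%) | 19 |
| 9.3% at each visit, independent | 140 × (1 − 0.907³) = 35.5 | about 35 (25%) | about 35, since 140 × 0.093³ = 0.1 miss all three |
| 9.3% at each visit, no overlap | 3 × 13 = 39 | 39 (28%) | 39 |

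**4. Precision.** No secondary outcome was powered, so the primary outcome's effect of 7/13 serves only as a yardstick. Power = Φ(7/(13√(2/n)) − 1.96), with n per arm: 89.0% at 140 patients, 85.9% at 127, 84.1% at 121, 82.1% at 114 and 79.9% at 108. The loss is modest.

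**5. Bias, by illustration.** Assume no true difference, scores in SD units with higher meaning worse, 9.3% random loss at week 4, and a later loss of proportion m in each arm. In one arm the later loss is random. In the other it falls only on the half with the poorer week-4 response, each with probability 2m. The expected complete-case week-4 difference is −2m × 0.399/(1 − m):

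- m = 0.05: −0.040/0.95 = −0.04 SD
- m = 0.10: −0.080/0.90 = −0.09 SD
- m = 0.15: −0.120/0.85 = −0.14 SD

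A simulation of 2,000 trials per setting gave the same figures (−0.041, −0.093, −0.140). Using all observed week-4 scores, the difference was about 0 throughout.

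**6. Total against subscales.** Mean baseline subscales among the 127 (Additional file 5): 4.57 + 1.57 + 13.13 = 19.27, against a total of 19.26. They are parts of the same score. With imputation the total can be analysed on up to 140 patients; without it the subscales can be analysed on at most 127.

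**The case against.** Nowhere does the SAP say that patients with a missing visit are dropped, and Mauchly's test is mentioned only for the primary outcome. This is correct: deletion is an inference. But the named method is the same, and no route is described by which a partly observed patient could contribute, so the inference is the natural reading.

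A reader might infer that the plan contradicts its own ITT definition. The documents do not support that. The all-available-data wording in section 5 is attached to the primary analysis. Only section 8's general statement reaches the secondary outcomes, and it does not repeat that wording. What stands is tension with a general commitment.

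A reader might also take 9% to 25% as the range of loss caused by choosing ANOVA. It is not. At the 9% end the method costs nothing, and 25% is one assumed pattern that equal missed-visit rates without overlap already exceed. Nor is a patient lost from every analysis, only from that of the incomplete outcome.

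Additional file 6 does compare the WOMAC subscales at week 4 on all 127 patients who provided week-4 WOMAC. That partly answers the point for the subscales. However, it is labelled per protocol, SAP section 9 plans such an analysis only for the primary outcome, and the file does not cover NRS, SF-12 or PGA.

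Finally, week-4 loss was balanced between arms, and baseline WOMAC total was similar in those without and with the outcome (18.85 and 19.26), although the proportion of Han ethnicity differed (76.92% and 96.06%, p = 0.027). With 13 patients this settles little, and baseline comparisons cannot show whether later loss depends on response.

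**Conclusion.** The point holds as a gap with a cheap remedy, confined to secondary outcomes. As written, the WOMAC subscales, NRS, SF-12 and PGA would be analysed on patients with complete visits, and observed scores from the others would be discarded.

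How much is lost cannot be determined from the documents, because attrition at weeks 8 and 16 is not reported. The avoidable exclusions are none if the same 13 patients miss every visit, and about 35 of 140 if 9.3% are missing independently at each of three visits. Neither bound is established by the plan.

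The loss of power is modest under these assumptions, and the possible bias matters more. The bias of 0.04 to 0.14 SD rests on response-related loss in one arm only and shows what could happen, not what did. The sample size is unaffected.

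**What to change.** In SAP section 8, analyse the WOMAC subscales, NRS and SF-12 with a linear mixed model on weeks 4, 8 and 16: group, visit, group × visit, the baseline value as covariate, and an unstructured covariance. Report the between-group difference at each visit. This uses every observed visit under missing at random and needs no sphericity test. Alternatively, extend the multiple imputation of section 10 to these outcomes. Either way, state the missing-data assumption and the number of patients contributing at each visit.

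For PGA, first reconcile the documents. The amended protocol defines change from baseline and its Table 4 marks a baseline collection, whereas SAP section 7 lists weeks 4, 8 and 16 only. The question put to patients asks about change since treatment began, so a baseline term has no meaning under that wording. If it stands, use the same model without the baseline covariate.

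The cost is SAP wording and slightly more analysis work. The named software has a mixed-model procedure, and no new data are needed.

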## 9. Statistical Methods – Sensitivity analyses

A sensitivity analysis will estimate treatment effects on the primary outcome at 4 weeks assuming only patients who completed the treatment without major protocol violations at week 4. The sensitivity analysis will be based on t-tests for continuous variables and chi-squared tests for categorical variables

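### The three performance tests and the week-4 per-protocol check leave out baseline as a covariate: valid, but less precise, and in the check population and method change together

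*Supplement*

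**What the plan says.** **Performance tests.** SAP section 7 defines the chair rise, Timed Up and Go (TUG) and One Leg Standing outcomes as change from baseline to week 4. Table 4 of the amended protocol schedules all three at baseline and week 4 (for example the row "Change in Timed Up and Go Test Time"), and SAP section 6 lists them among the baseline characteristics. For their analysis SAP section 8 states "30 Second Time Chair Rise Test, TUG and One Leg Standing Test will be applied with an independent t test for normal distribution", with a Mann-Whitney U test if the data are not normal. No covariate is named.

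**Primary analysis.** The same section analyses WOMAC total by repeated measures ANOVA over all visits, with age, sex, BMI, baseline WOMAC and medication as covariates. If the group-by-time interaction is not significant, the treatment main effect is tested next. SAP section 10 adds multiple imputation for the primary outcome.

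**Per-protocol check.** SAP section 9 re-estimates the week-4 effect on the primary outcome in patients who finished treatment with no major violation: "The sensitivity analysis will be based on t-tests for continuous variables and chi-squared tests for categorical variables". Again no covariate is named.

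**The concern.** Subtracting the baseline is not the same as adjusting for it. A change score fixes the slope on baseline at 1. When the correlation between baseline and week 4 is below 1, that over-corrects, leaves avoidable noise in the estimate, and lets a chance baseline imbalance move it in the particular sample. The SAP uses baseline as a covariate for the primary outcome and gives no reason for not doing so here.

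The One Leg Standing Test is a special case. The amended protocol stops the clock at 30 seconds. Among patients who provided the primary outcome, the baseline mean is 18.76 s (SD 10.63, Additional file 5), so one SD above the mean is 18.76 + 10.63 = 29.39 s, almost at the cap. A patient at the cap cannot improve, so the change depends mechanically on the starting value. The Mann-Whitney fallback yields no baseline-adjusted estimate.

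For the per-protocol check the issue is interpretation. A reader will set it beside the primary result to see whether non-adherence matters. If the model, the covariates and the handling of missing data also differ, neither agreement nor disagreement can be traced to the population.

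**Working it through.** **1. The plan's own sample size.** Inputs from protocol section 4 on target numbers: "mean difference of 7 to mPT with a standard deviation for both groups of 13", two-sided alpha 0.05, power 80%, compliance 80%.
- Normal approximation: 2 × (1.960 + 0.842)² × 13² / 7² = 54.1, so 55 per arm. With the t distribution, 56 per arm.
- 56 / 0.8 = 70 per arm, 140 in total, as stated. No gain from covariates was assumed.

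**2. Performance tests.** With equal SD s at both visits and correlation r, the per-patient variances are 2s²(1−r) for change and s²(1−r²) for ANCOVA. Their ratio is (1−r²) / [2(1−r)] = (1+r)/2. The documents give no r for these tests, so a range is assumed:

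| r (assumed) | ANCOVA / change variance | Variance saved | Extra patients needed by the change t test | CI width, change / ANCOVA |
|---|---|---|---|---|
| 0.3 | 0.65 | 35% | 54% | 1.24 |
| 0.5 | 0.75 | 25% | 33% | 1.15 |
| 0.7 | 0.85 | 15% | 18% | 1.08 |
| 0.8 | 0.90 | 10% | 11% | 1.05 |
| 0.9 | 0.95 | 5% | 5% | 1.03 |

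**3. Per-protocol check, WOMAC total.** Inputs from Additional file 6 (63 Tuina, 64 mPT): baseline SDs 13.52 and 13.62; week-4 SDs 12.46 and 12.70; change −5.65 (−8.33, −2.97) and −5.84 (−9.56, −2.12).
- SD of change = half-width / t × √n. Tuina: 2.68 / 1.999 × √63 = 10.64. mPT: 3.72 / 1.998 × √64 = 14.89.
- r = (SD₀² + SD₄² − SD_change²) / (2 × SD₀ × SD₄). Tuina 0.67, mPT 0.36.
- Pooled within-arm variances: baseline 184.2, week 4 158.3, change 167.9. Covariance = (184.2 + 158.3 − 167.9) / 2 = 87.3. Pooled r = 0.51; slope on baseline = 87.3 / 184.2 = 0.474.
- Change t test: SE = √167.9 × √(1/63 + 1/64) = 2.30, half-width 4.55. This recovers the reported interval (−4.36, 4.74).
- ANCOVA: residual variance = (158.3 − 87.3²/184.2) × 125/124 = 117.9; SE = 1.93; half-width about 3.81.
- Variance ratio 117.9 / 167.9 = 0.70, about 30% less; the interval is about 16% narrower.
- Adjusted difference = −0.13 − 0.474 × (−0.33) = about 0.03.

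**4. What changes between the two analyses of the primary outcome.**

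| | Primary (SAP 8 and 10) | Check (SAP 9) |
|---|---|---|
| Population | ITT | Finished treatment, no major violation |
| Model | Repeated measures ANOVA, all visits | t-test |
| Covariates | Age, sex, BMI, baseline WOMAC, medication | None |
| Missing outcome | Multiple imputation | None specified |
| Target | Week-4 difference, or main effect over time if no interaction | Week 4 |

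**The case against.** **Validity.** The unadjusted tests are sound. Baseline is subtracted, not ignored, and a change-score t test is unbiased under randomisation. A reader might infer bias or an inflated type I error; nothing in the plan supports that. The influence of chance imbalance is a feature of the single sample, not a systematic error. This stands.

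**Size for the performance tests.** A reader might carry the 30% for WOMAC over to them, or apply the two arms' correlations separately as a range for the trial. Neither is supported. The documents hold no correlation for these tests, the gain is only 5% at r = 0.9, and a two-arm comparison has one pooled ratio.

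**Consequence.** The sample size assumed no covariate gain, and the pooled SD of change recovered above (√167.9 = 12.96) is close to the assumed 13, so an unadjusted comparison is not underpowered against its own design. Baseline WOMAC differs by only 0.33 points. The unadjusted interval (−4.36, 4.74) and the adjusted one (about −3.78 to 3.84) both exclude a difference of 7 in either direction. A reader might expect adjustment to change the conclusion; for WOMAC the reported figures suggest it would not.

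**Purpose of the check.** SAP section 9 does not claim to isolate the effect of violations. A simple comparison in completers still shows whether the conclusion survives a change of population and model, so calling it useless goes too far. What remains is that a discrepancy could not be assigned to one cause. Section 9 also names t-tests only for continuous outcomes; Mann-Whitney belongs to the performance tests.

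**Conclusion.** The point holds as a matter of precision and interpretability, not of validity.

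- **Performance tests.** Leaving baseline out as a covariate gives up precision at any correlation below 1. The amount is unknown: about 25% of the variance at r = 0.5, 10% at 0.8 and 5% at 0.9, assuming equal SDs at the two visits.
- **Per-protocol check.** Population and method change together, so a difference from the primary result could not be attributed to protocol violations alone. For WOMAC total, baseline adjustment would cut the variance by about 30% (half-width 4.55 to about 3.8). This rests on the rounded figures in Additional file 6 and on one slope common to both arms, although the implied correlations differ (0.67 and 0.36). It uses results only to show the size; the finding itself rests on the SAP text.

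The case for matching the check to an adjusted ITT contrast is the stronger of the two. The performance-test change is an efficiency gain for secondary outcomes at almost no cost.

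**What to change.** **SAP section 8.** Analyse each performance test by ANCOVA of the week-4 value on group and that test's own baseline, and report the adjusted mean difference with its 95% CI. For the One Leg Standing Test use a rank-based ANCOVA or a bootstrap interval because of the 30-second cap.

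**SAP section 9.** Define the check as a between-group contrast in WOMAC total at week 4, adjusted for age, sex, BMI, baseline WOMAC and medication. Report the same contrast in the ITT set, and state one missing-data rule for both, so that only the population differs. Simply rerunning the primary model as written would not do: it has baseline both as a covariate and as a level of time, and without a significant interaction it tests a main effect over time instead of week 4.

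**Cost.** A few sentences in the SAP and a re-run on data already collected. As results are already reported, the added analyses should be labelled post hoc.
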